### Data management

Following study completion all data will be linked-anonymized, with the linking documents being kept on separate encrypted drives. Fully anonymized data will be made open access through managed open access following the publication of our findings. That is, any researcher will be provided with our data if they consent to adhere to the General Data Protection Regulation and the British Psychological Society’s Code of Ethics and Conduct. Our consent procedure will inform participants of these data storage and sharing procedures.

### Statistical analyses

Statistical analyses will be performed using
R
^76^. Prior to all hypotheses testing, the two training groups will be compared on age using a Bayesian
*t*-test to ensure that stratification was successful. The groups will then be compared on the following potential confounds using non-parametric Chi-square tests for binary and general linear modelling for continuous variables: gender, parental education, pubertal stage, intelligence, time interval between pre- and post-training (days); testing location and testing groups size to experimenter ratio. Any variables showing significant group differences at baseline will be added to all subsequent group comparisons as covariate.

Next, we will explore the structure of our outcome measures of interest at baseline. Specifically, we will explore the structure of affective and cognitive functioning using structural equation modelling (SEM). We hypothesize that cognitive control is best modelled using separate factors for affective, versus neutral, item content, such that the model in
Figure 4 will outperform a single-factor model.

**Figure 4. f4:**
[figure not shown]
Predicted structure of affective and cognitive functioning at baseline. The figure offers a schematic representation of the predicted structure of cognitive and affective control in adolescents. Raven’s i1 – 12 = items 1 – 12 on the Raven’s Advanced Progressive Matrices; d’ = d prime on backward digit span; RT = reaction time; rE = proportion random errors; Acc = percentage trials correct. Rectangular boxes = measured variables; ovals = latent constructs.

To investigate the first hypothesis (
*affective control training hypothesis*) we will use mixed effects modelling with training group as fixed effect and time as within-subject effect. The outcome of interest will be
*d*’ achieved on the affective
*n*-back task. Additionally, we will explore the impact of training on reaction time as a secondary outcome of interest. For the secondary analyses to be considered significant, we will apply a Bonferroni correction to reduce the threshold for statistical significance for two comparisons (accuracy and reaction) to α ≤ .025. We will then explore whether any effects of group and time are moderated by total training time (mins), total number of individual training sessions and ratio of time spent training on training task C relative to A and B. We plan to include these overlapping measures separately as they arguably provide different types of information. Specifically, total training time will allow us to explore dose-response relationships. The other two measures, we propose, index more motivational factors such as diligence and/or motivation by the monetary incentive. To facilitate interpretation of any potential moderating effect, we will use a SEM trees approach to these moderators and enter the relevant groupings as moderators. We will additionally investigate the effect of time spent on each training version separately on the outcome of interest and compare the effect of time spent on the single versions versus time spent on the dual version.

Our second hypothesis (
*affective control facets hypothesis*), that AffeCT will improve inhibition, updating and shifting, will be tested with a multivariate mixed effects model. Time and group will be included as fixed effects and the three measures of affective control as outcomes of interest (i.e., working memory updating, inhibition, and set-shifting). The primary outcome of interest is accuracy, as this has been shown to be a more sensitive than reaction time in dissociating between individuals with and without mental health problems
^7^. As with the first hypothesis, we will investigate whether any training benefits are moderated by total training time (mins), total number of individual training sessions or time spent training on task C relative to A and B. The analyses will be repeated with reaction time as a secondary outcome of interest.

Our
*age-related change hypothesis*, will be tested by including age a moderator in the multivariate mixed effects model used to test the
*affective control training hypothesis*. The potentially moderating effect of age will be investigated using SEM trees. SEM trees identify age groupings to the benefits conferred by training. While the exploration is data-driven, it is theoretically informed by the literature showing differential effects of cognitive training on young compared to older adolescents
^34^. A second exploratory analysis will include age as a continuous variable in the same model to investigate any linear or polynomial effects of age.

Fourth, to test the
*mental health hypothesis,* we will use latent change score models, a subclass of SEM approaches
^77^, which naturally allows for the integration of predictors of rates of change (e.g. improvements in mental health). Specifically, we will investigate whether pre- to post-training changes in the affective control factor established at baseline are associated with fewer self-reported mental health problems and emotion regulation difficulties, as well as higher levels of self-reported self-control at each assessment time point. The primary analyses will include the post-training and one-month follow-up assessment. Secondary analyses will include the one-year follow-up.

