## Abstract

**Background: **75% of all mental health problems have their onset before the end of adolescence. Therefore, adolescence may be a particularly sensitive time period for preventing mental health problems. Affective control, the capacity to engage with goal relevant and inhibit distracting information in affective contexts, has been proposed as a potential target for prevention. In this study, we will explore the impact of improving adolescents’ affective control capacity on their mental health.

**Methods: **The proof-of-principle double-blind randomized controlled trial will compare the effectiveness of an app-based affective control training (AffeCT) to a placebo training (P-Training) app. In total, 200 (~50% females) adolescents (11-19 years) will train for 14 days on their training app. The AffeCT will include three different
*n*-back tasks: visuospatial, auditory and dual (i.e., including both modalities). These tasks require participants to flexibly engage and disengage with affective and neutral stimuli (i.e., faces and words). The P-Training will present participants with a perceptual matching task. The three versions of the P-Training tasks vary in the stimuli included (i.e., shapes, words and faces). The two training groups will be compared on gains in affective control, mental health, emotion regulation and self-regulation, immediately after training, one month and one year after training.

**Discussion: **If, as predicted, the proposed study finds that AffeCT successfully improves affective control in adolescents, there would be significant potential benefits to adolescent mental health. As a free app, the training would also be scalable and easy to disseminate across a wide range of settings.

**Trial registration: **The trial was registered on December 10th 2018 with the International Standard Randomised Controlled Trial Number (Registration number:
ISRCTN17213032).

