^33^. However, given that affective control in particular may be impaired in adolescents with high levels of mental health problems, we will trial the effect of an affective control training (AffeCT) paradigm in our forthcoming study. Specifically, we will explore whether AffeCT improves adolescents’ mental health and emotion regulation capacity and whether the magnitude of these improvements differs as a function of age.

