*n*-back task across the two training groups.2. AffeCT compared to P-Training will lead to greater improvements in all facets of affective control as measured by non-trained affective control tasks, including affective inhibition, updating and shifting tasks (
*affective control facets hypothesis*).3. The benefits of AffeCT will vary as a function of age (
*age-related change hypothesis*).4. Increases in affective control from pre- to post-training will be associated with fewer self-reported mental health problems and emotion regulation difficulties, as well as higher levels of self-reported self-control, at each assessment time point (
*mental health hypothesis*).

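### The article announces a between-arm comparison on mental health, emotion regulation and self-regulation, but its statistical section specifies none: these outcomes are only related to each participant's own change in affective control

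*Protocol article*

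**What the plan says.** The Abstract of the protocol article promises a comparison by arm: "The two training groups will be compared on gains in affective control, mental health, emotion regulation and self-regulation, immediately after training", and again at one month and one year. The Background gives the purpose in the same terms: "we will explore whether AffeCT improves adolescents’ mental health and emotion regulation capacity". It adds the question of age differences in those improvements ("mental health and emotion regulation capacity and whether the magnitude of these improvements differs as a function of age"). The section The present study says the self-report measures are collected to look for benefits of AffeCT.

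The fourth hypothesis, listed in that section, is worded differently: "Increases in affective control from pre- to post-training will be associated with fewer self-reported mental health problems and emotion regulation difficulties". It claims an association and contrasts no arms.

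Under Statistical analyses, the model for the first hypothesis names the arm: "we will use mixed effects modelling with training group as fixed effect and time as within-subject effect". So does the model for the second: "Time and group will be included as fixed effects and the three measures of affective control as outcomes of interest". The third adds age to an affective control model. For the fourth, latent change score models are chosen, a method "which naturally allows for the integration of predictors of rates of change (e.g. improvements in mental health"). The next sentence then fixes the test: "we will investigate whether pre- to post-training changes in the affective control factor established at baseline are associated with fewer self-reported mental health problems", with parallel wording for emotion regulation difficulties and self-control. Post-training and one month are primary; one year is secondary.

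**The concern.** Whether AffeCT improves mental health is a question about randomised arms. The stated analysis asks something else: whether participants whose affective control rose more, for whatever reason and in either arm, report better mental health. Maturation, motivation or mood on the testing day can move both task performance and self-report, and randomisation does not balance such influences across levels of a variable measured after allocation.

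Two things are at stake. A significant association could be reported as a mental health benefit of AffeCT when the arms do not differ. And a real difference between arms on the self-report scales has no specified test, although randomised data to test it will be collected.

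**Working it through.** **Step 1. Outcomes and terms in each stated analysis.**

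| Analysis | Outcome | Training group named? |
|---|---|---|
| Hypothesis 1 | n-back *d*', reaction time secondary | Yes |
| Hypothesis 2 | inhibition, updating, shifting | Yes |
| Hypothesis 3 | affective control model with age as moderator | Through the model it extends |
| Hypothesis 4 | self-reported mental health, emotion regulation, self-control | No |

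The self-reports appear only in the last row, so the comparison announced in the Abstract has no specified analysis. Age differences in mental health gains, raised in the Background, have none either.

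**Step 2. The plan's own power figure.** The article gives at least 93% power with 100 per arm and *d* = 0.40, for the first hypothesis only. Assume two-sided α = 0.05 (not stated for this calculation) and power = Φ(*d* / (s·√(2/100)) − 1.96), where s is the SD of the analysed score in baseline SD units and *r* the pre-post correlation.
- Post-score only, s = 1: 0.40/0.1414 = 2.83, power 80.7%.
- Change score, s = √(2(1−*r*)): 80.7% at *r* = 0.5 and 92.9% at *r* = 0.66.
- Baseline-adjusted, s = √(1−*r*²): 90.4% at *r* = 0.5 and 94.2% at *r* = 0.6.

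So 93% is reachable, but the variance components entered in the calculator are not given, and the figure can be neither confirmed nor called wrong. It does not cover the mental health outcomes, and this point does not depend on it.

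**Step 3. What the stated association can show.** In a simulation of 4,000 trials with 100 per arm, AffeCT raised affective control by 0.4 SD, the arm effect on mental health was zero, and the change in control and the mental health score correlated within arm at ρ for non-training reasons. Signs are set so that better control goes with fewer problems.

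| Assumed ρ | Association significant | Arm comparison significant |
|---|---|---|
| 0 | 4.7% | 4.4% |
| 0.1 | 28% | 5.2% |
| 0.2 | 81% | 5.1% |
| 0.3 | 99% | 5.2% |

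Fisher's z gives a check: power = Φ(atanh(ρ)·√197 − 1.96). For ρ = 0.1, 0.2, 0.3 the first term is 1.41, 2.84, 4.34, so power is 0.29, 0.81, 0.99. The arm shift slightly dilutes the pooled correlation (by 1/√1.04), which changes little: 0.28, 0.80, 0.99.

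**Step 4. What an arm comparison could detect.** Baseline-adjusted formula of step 2, 100 per arm, no dropout:

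| True *d* | *r* = 0 | *r* = 0.5 | *r* = 0.7 |
|---|---|---|---|
| 0.20 | 29% | 37% | 51% |
| 0.30 | 56% | 69% | 84% |
| 0.40 | 81% | 90% | 98% |

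The detectable *d* at 80% power is 0.40, 0.34 and 0.28 respectively.

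**The case against.** The best defence is that the fourth hypothesis is deliberately about mechanism. The Abstract and Background also describe the study as exploring what improving affective control does for mental health; the trial is called proof-of-principle and is powered only for the first hypothesis. Hypothesis and analysis agree with each other. This stands as a description of the fourth hypothesis, but it leaves the comparison announced in the Abstract without a test.

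A second defence is that silence is not exclusion. Latent change score models can carry predictors, and supplementary methods not available here may add the arm. A reader might infer that the trial will never test the effect of AffeCT on mental health. The document does not support that, since the Abstract announces the comparison; it supports only that no such test is specified. The defence goes no further, because the article does more than omit detail: it spells out the test as an association after naming group for the first two hypotheses.

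Third, the percentages in step 3 are the power to detect a correlation that was assumed to exist. They are not false-positive rates for the fourth hypothesis, which claims exactly such a correlation, and the values of ρ have no source in the article. A reader might also picture AffeCT having no effect on anything and the trial still being declared a success. In that case the randomised tests of the first two hypotheses would be null apart from chance, and a lone positive association would hardly pass as benefit. The scenario that matters is the one simulated: a real effect on control and none on mental health.

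Fourth, lack of time order is a problem only at the post-training assessment. At one month, also primary, the change in control precedes the outcome. Confounding remains at both.

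**Conclusion.** The point holds as an internal contradiction: the comparison announced in the Abstract and implied by the Background has no counterpart under Statistical analyses, and the one analysis of these outcomes rests on a post-randomisation variable without naming the arm. Followed as written, it answers a randomised question with evidence open to confounding, and a positive result cannot establish that AffeCT improves mental health. The contradiction needs no numerical assumption. The size is illustrative: it rests on the assumed within-arm correlations, a simple correlation in place of the latent change model, two-sided α = 0.05 and no dropout.

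**What to change.** Under Statistical analyses, add training group as a predictor of change in Strengths and Difficulties total difficulties, DERS total and the Brief Self-Control score, in all participants as randomised, and state that this arm effect is the test of benefit. Three scales at two primary time points make six arm tests; at 5% each, the chance of at least one false positive would be 1 − 0.95⁶ = 26% if they were independent. So name one scale and one time point as primary, or set a multiplicity correction across scales and primary time points, with one year secondary.

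Keep the association as a secondary mechanism analysis with arm in the model, and say that including arm does not remove confounding within arms. If no arm comparison is intended, narrow the Abstract and Background instead.

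The cost is one group path per model, a rewording of the fourth hypothesis and a few extra tests, with no new data. At this protocol version no participant had completed training or a post-training assessment, so the change could have been made before any outcome was seen. The drawback is power: about 29–51% at *d* = 0.20 and 81–98% at *d* = 0.40 for assumed pre-post correlations of 0 to 0.7, less with dropout. The plan should say so, because a null result would not exclude a small benefit.

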## Research ethics approval

Ethical approval for this study has been conferred by the University College London (UCL) Research Ethics Committee on 23 April 2018; Project ID:12753/002. Any protocol amendments will be submitted to the UCL Research Ethics Committee Chair for approval and recorded on
the Open Science Framework pre-registration documentation.

## Consent and assent procedures

Assent and consent will be obtained from prospective participants and their legal guardians, respectively. For participants under 18 years, study information and consent forms will first be sent to the parents. Parents will then have the opportunity to read the information and contact the research team with any potential questions. Children of parents who provide consent will be asked to provide written informed assent. Participants aged 18 years and over will be asked to provide written informed consent. When participants are tested at the pre- and post-training assessments they will be reminded that they can withdraw consent at any time before, during or after the study without any consequence and that they will be compensated for any part of the study completed until withdrawal.

## Availability of data

Consent from participants will be obtained to share data through managed access. Researchers wishing to access the data need to consent to storing and analyzing the data in line with the General Data Protection Regulations and the British Psychological Society’s Code of Ethics and Conduct.

## Dissemination policy

The study has a multi-component dissemination policy: academic, stake-holders and public.

**Academic.** Standard academic dissemination of the study results will be sought through journal publications. Findings will also be communicated at scientific conferences and where permitted by journal regulations published on pre-print archives.

**Stakeholders.** Findings will be communicated via email to all research participants in a newsletter style communication. The main trial outcome paper will also be submitted as a
*Frontiers for Young Minds* article and if accepted sent to all participants. We will further present the findings during a school talk in any of the participating schools that are interested in this option.

**Public.** The findings will also be communicated to the public by presenting them at public talks as well as through social media and, if interest can be generated, conventional broadcast or print media.

## Trial status

The trial data collection started 21 September 2018 and the funding end date for this trial is 08 January 2022. Pre-training assessments have been completed in 64 participants, but none of these participants have completed training or any post-training assessments. This is protocol version 1 (30 November 2018).

## Conclusions

If, as predicted, the proposed study finds that AffeCT successfully improves affective control in adolescents, there would be significant potential benefits to adolescent mental health. As a free app, the training would also be scalable and easy to disseminate across a wide range of settings.

## Data availability

### Underlying data

No data are association with this article.

### Extended data

Open Science Framework: Protocol for an App-Based Affective Control Training for Adolescents.
https://doi.org/10.17605/OSF.IO/6THSN
^44^

This project contains the following extended data:

-Supplementary Materials - WOR.pdf (Additional methods to main manuscript and completed SPIRIT checklist)

### Reporting guidelines

Open Science Framework: SPIRIT checklist for Protocol for an App-Based Affective Control Training for Adolescents.
https://doi.org/10.17605/OSF.IO/6THSN
^44^

Data are available under the terms of the
Creative Commons Zero "No rights reserved" data waiver (CC0 1.0 Public domain dedication).
